## Methods/design

### Study design

VIDEO is a randomized, placebo-controlled double-blind clinical trial. Four hundred subjects (200 from Tasmania and 200 from Victoria) with symptomatic knee OA and serum 25-(OH)D > 12.5 nmol/liter and < 60 nmol/liter will be recruited and randomly allocated to either the treatment or placebo control group. Recruitment methods will include advertisements through the local media and community groups as well as liaisons with general practitioners, specialist rheumatologists, and orthopedic surgeons. Ethics approval has been received from The Tasmania Health and Human Medical Research Ethics Committee (reference number H1040) and Monash University Human Research Ethics Committee (reference number CF10/1182 - 2010000616). Informed written consent will be obtained from all participants.

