### Randomization

Participants in each site will be randomly assigned to the intervention arm or placebo arm in a ratio of 1:1 and the randomization will be double-blind. Allocation of participants will be based on computer-generated random numbers. Allocation concealment will be ensured by the use of an identical inert placebo, and a central automated allocation procedure, with security in place to ensure allocation data cannot be accessed or influenced by any person.

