### Outcome measures

The co-primary efficacy endpoints of the study will be MRI assessment of volume changes in knee cartilage from baseline to month 24, as well as the Western Ontario and McMaster Universities Index of OA (WOMAC) score 
[31] (Table 
1). The secondary endpoints will be other knee structural changes (cartilage defects, tibial plateau bone area, and bone marrow lesions, meniscal tear and extrusion) from baseline to month 24, and lower limb muscle strength at months 3, 6, 12 and 24 (Table 
1). 

**Table 1 T1:** Timetable and measures to be made

	**Screening**	**Month(s)**				
		**0**	**3**	**6**	**12**	**24**

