### Analysis plan

Statistical primary comparisons for total and subscale WOMAC scores will be made using a repeated measures mixed model with terms for treatment, month, center and the corresponding baseline values as the covariates. The independent *t*-tests will be used to compare changes between groups in quantitative data from baseline to the end of follow-up. Linear regression (annual changes in cartilage volume, cartilage defects, bone area and muscle strength as the dependent variables, and treatment as the independent variable) and logistic regression (development/progression of bone marrow lesions and meniscal abnormalities as the dependent variables, treatment as the independent variable) analyses will be applied in univariate and multivariate modeling adjusted for age, sex, body mass index, baseline 25-(OH)D and other disease status.

In secondary analysis of loss in cartilage volume, the minimal clinically important differences (MCID) in cartilage volume will be calculated 
[47] and logistic regression will be used to determine the association between cartilage loss (> = MCID vs. < MCID) and treatment before and after adjustment for the covariates described above.

Both intention to treat and per protocol analyses will be utilized. Per protocol will be defined as achieving a 25-(OH)D level > 60 nmol/liter at month 3. The last observation carried forward method will be used in the analysis of all outcomes among patients who made at least one follow-up visit but did not complete the whole study.

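### The cartilage co-primary and other MRI models name neither centre nor the measure's baseline value, unlike the WOMAC model, and the deciding cartilage analysis is not named

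*Protocol article*

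**What the plan says.** The Study design section plans "Four hundred subjects (200 from Tasmania and 200 from Victoria". The Randomization section states: "Participants in each site will be randomly assigned to the intervention arm or placebo arm in a ratio of 1:1". Under Outcome measures the two co-primary endpoints are "MRI assessment of volume changes in knee cartilage from baseline to month 24" and the WOMAC score.

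The Analysis plan treats these two endpoints differently:

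- **WOMAC:** "repeated measures mixed model with terms for treatment, month, center and the corresponding baseline values as the covariates".
- **Cartilage volume and other quantitative changes:** "The independent *t*-tests will be used to compare changes between groups in quantitative data from baseline to the end of follow-up".
- **Cartilage volume and other continuous outcomes, by linear regression:** "annual changes in cartilage volume, cartilage defects, bone area and muscle strength as the dependent variables, and treatment as the independent variable".
- **Bone marrow lesions and menisci, by logistic regression:** "development/progression of bone marrow lesions and meniscal abnormalities as the dependent variables, treatment as the independent variable".

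The regressions are run without covariates and then "adjusted for age, sex, body mass index, baseline 25-(OH)D and other disease status". The secondary logistic analysis of cartilage loss at or above the MCID reuses that covariate list. The article describes a primary comparison only for WOMAC.

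**The concern.** The article sets out two covariate lists for two co-primary endpoints, and they differ without a stated reason. Centre and baseline value are in the first list and absent from the second, although patients are randomised within site and every participant is scheduled for a baseline MRI.

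Two things are at stake:

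- **Precision and chance imbalance.** If site or baseline volume predicts cartilage change, leaving it out keeps that variation in the error term. Any chance difference between arms in baseline volume then stays in the treatment estimate.
- **Choice of result.** The cartilage co-primary has both an unadjusted and an adjusted analysis, and the article does not say which one carries the conclusion.

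**Working it through.** **Inputs.** From Table 2 of the Sample size section: difference 2.16 percentage points, SD 6.5, 143 per arm. From the same section: α = 0.05, β = 0.20, 200 per arm, 20% dropout. Completers: 200 × 0.80 = 160 per arm. The article does not state sidedness; two-sided is used because it reproduces the stated figure.

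**Step 1: reproduce the plan's figure.**
n = 2 × (1.960 + 0.842)² × 6.5² / 2.16² = 142.2, rounded up to 143. This equals the stated 143 (a one-sided test would give 112). The sample size therefore rests on an unadjusted two-group comparison and does not depend on any covariate.

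**Step 2: power as planned.**
SE = 6.5 × √(2/160) = 0.727. Power = Φ(2.16/0.727 − 1.960) = Φ(1.012) = 84.4%.

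**Step 3: power with centre and baseline in the model.** Let R² be the share of outcome variance that the two explain together. The article gives no value, so a range is assumed. The residual SD is 6.5 × √(1 − R²), and the equivalent number of completers is 160/(1 − R²).

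| Assumed R² | SE relative to unadjusted | Equivalent completers per arm | Power, 160 per arm | n per arm for 80% power |
|---|---|---|---|---|
| 0 | 1.000 | 160 | 84.4% | 143 |
| 2% | 0.990 | 163 | 85.1% | 140 |
| 5% | 0.975 | 168 | 86.2% | 136 |
| 10% | 0.949 | 178 | 88.0% | 128 |

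**Step 4: how much centre alone could explain.** With two equal centres whose mean cartilage loss differs by D points, R² ≈ (D/2)²/6.5².

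- D = 1: 0.25/42.25 = 0.6%.
- D = 2: 1/42.25 = 2.4%.
- R² = 5% needs D = 2 × 6.5 × √0.05 = 2.9 points.
- R² = 15% needs D = 2 × 6.5 × √0.15 = 5.0 points.

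Table 2 gives a mean loss of 4.5% and a target difference of 2.16. A site effect large enough for 5% would exceed the target treatment effect, and one large enough for 15% would exceed the mean loss itself.

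**Step 5: type I error of the unadjusted test.** If allocation is forced into balance within site, the true level is 2 × [1 − Φ(1.960/√(1 − R²))]. For a 2-point site difference (R² of 2.0% to 2.4%) this is about 4.8% to 4.7%. If allocation within site is simple randomisation, the unadjusted test keeps its nominal 5% level over repeated randomisations.

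**Step 6: number of competing analyses.** A t-test of change and a regression of change on a two-level treatment term are the same test when follow-up is equal, because annualising only rescales the outcome. They can part for early withdrawers, whom the Withdrawal section asks to have an MRI at the end of year 1 or on leaving. In substance there are two analyses to rank, unadjusted and adjusted.

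**The case against.** On the other side, the outcome is within-person change, expressed as a percentage in Table 2, so baseline is already subtracted and scaled. The covariate list also ends with an undefined item on other disease status that might take in baseline structure. Nothing in the article shows that baseline volume predicts percentage change. Both sites follow one imaging description, so a scanner or case-mix difference is only a possibility. Naming the primary model may be left to a statistical analysis plan that is not shown.

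Much of this stands, and it limits the size of the point. It does not remove it. Computing a change is not the same as adjusting for baseline, and other disease status cannot mean centre. The article is also not silent: it gives a list for each co-primary, and the two do not match.

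A reader might go further and infer that the standard errors and p-values for cartilage are wrong because the randomisation stratum is ignored, with a true type I error well under 5%. The article does not support this. The Randomization section mentions computer-generated numbers and central allocation but no blocking, and a large shift would need the implausible site differences in Step 4. A reader might also count three competing analyses; Step 6 shows that there are essentially two.

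**Conclusion.** The point holds as an inconsistency that costs some efficiency. The cartilage co-primary and the other MRI models name neither centre nor the measure's baseline value, although the WOMAC model has both, and the deciding cartilage analysis is not identified.

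The loss is modest: about 0.7 to 3.5 percentage points of power with 160 completers per arm (85.1 − 84.4 to 88.0 − 84.4, from unrounded values), if centre and baseline together explain 2% to 10% of the variance. That range is an assumption. Chance imbalance in baseline volume would also go uncorrected.

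It should not be read as bias, inflated type I error or an underpowered trial. The stated 143 per arm reproduces without adjustment, and 160 completers give more than 80% power. Any effect on the test level is in the conservative direction, is small, and arises only if allocation is blocked within site. This is a free improvement, not a defect that threatens the trial's conclusions.

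**What to change.** - Name one primary analysis for the cartilage co-primary: a linear model of change on treatment, centre and the baseline cartilage volume of the plate analysed. Keep the listed age, sex, BMI and baseline 25-(OH)D, and state what other disease status comprises.
- Add centre and the outcome's own baseline value to the other MRI linear and logistic models. In the MCID model the baseline term is baseline cartilage volume.
- Label the t-test and the unadjusted fits as supportive.

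The cost is wording only. Site is known for every participant and baseline MRI is in the Table 1 schedule, so no new data and no change to the sample size are needed. The article reports recruitment as still under way, so the change can be written into the analysis plan before unblinding.

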[18]. Magnetic resonance imaging (MRI) has been utilized to directly assess knee structural alterations such as cartilage volume, cartilage defects, subchondral bone changes and meniscal lesions. Using MRI, we reported that, in cross-sectional analysis, serum 25-(OH)D level was significantly and positively associated with knee cartilage volume in older men and women, and vitamin D insufficiency was positively associated with medial and lateral tibial bone area in women. Longitudinally, higher baseline serum levels of 25-(OH)D predicted reduced loss of cartilage volume over 2 years, and increases in vitamin D levels were associated with further protective association 
[15,16]. Furthermore, serum levels of 25-(OH)D were also associated with increased leg muscle strength and quality, and thus may be important for the maintenance of muscle function 
[20].

Based on this experimental and epidemiological evidence, we have initiated a randomized, placebo-controlled trial (Vitamin D Effect on Osteoarthritis, VIDEO study) to determine if vitamin D supplementation can reduce loss of knee cartilage volume, prevent the progression of other knee structural abnormalities and strengthen lower limb muscle strength, and thus modify disease progression in knee OA. The effects of vitamin D supplementation on the progression of knee pain will also be determined.

In a sub-study, we will examine the effects of vitamin D supplementation on the function of deep lumbo-pelvic stabilising muscles. The protective deep lumbo-pelvic stabilising muscles, which include (but not exclusively) the transversus abdominus (TrAb) and lumbar multifidus and which are known as core muscles, become dysfunctional shortly after the onset of low back pain, and that ongoing muscle dysfunction is associated with persistent low back pain 
[18,21]. Muscle weakness can be a sign of vitamin D deficiency 
[19] and therefore, vitamin D supplementation may have beneficial effects on functionally important core muscles.

Furthermore, we will determine the effect of vitamin D supplementation on blood pressure (clinical, ambulatory, upper arm and central measures) and arterial stiffness (aortic pulse wave velocity). Several lines of evidence suggest that vitamin D deficiency may influence blood pressure via mechanisms including activation of the renin-angiotensin-aldosterone system (RAAS) 

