### Inclusion criteria

The inclusion criteria were as follows: age 50 to 79 years; symptomatic knee OA for at least 6 months with a pain at least 20 mm on a 100 mm visual analogue scale (VAS); American College of Rheumatology (ACR) criteria for symptomatic knee OA assessed by a rheumatologist 
[27]; ACR functional class rating of I, II and III 
[28]; relatively good health, with a score of 0 to 2 on a 5-point Likert scale (with a range of 0 indicating very good health to 4 indicating very poor health), according to the investigators global assessment of disease status; serum 25-(OHD)D > 12.5 nmol/liter and < 60 nmol/liter; able to read, speak and understand English, capable of understanding the study requirements and willing to cooperate with the study instructions.

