### Intervention

Participants in the intervention arm will take one capsule per month of 50,000 IU (1.25 mg) of a vitamin D3 compound (cholecalciferol), purchased from Nationwide Compounding Pharmacy, Melbourne, Australia
[30], and patients in the control arm will receive an identical inert placebo provided by the same company. Patients are required to record their medication information in personal diaries and a reminder will be given each month. All participants will receive the recommended standard of care. The duration of the study is 2 years.

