**Other measures**						
Core musculature measure		✓			✓	✓
Hand grip strength		✓	✓	✓	✓	✓
Central and upper arm blood pressure		✓		✓	✓	✓
Aortic stiffness		✓		✓	✓	✓
Physical activity (IPAQ)		✓				✓
Body fat		✓			✓	✓
Low foot pain		✓	✓	✓	✓	✓
Low back pain		✓		✓	✓	✓
Depression		✓	✓	✓	✓	✓
Quality of life		✓		✓	✓	✓
Previous knee injury and occupation		✓				✓
Weight		✓	✓	✓	✓	✓
Height		✓				✓
Girth measurements		✓			✓	✓
Knee radiograph	✓					
Serum 25-(OH)D	✓		✓			✓
Serum calcium, phosphate, creatinine	✓		✓			
Sun exposure		✓		✓	✓	✓
Cigarette smoking		✓				✓
Diet (FFQ) and pedometer		✓				✓
Medications	✓	✓	✓	✓	✓	✓
Pill counts and adverse events		✓	✓	✓	✓	✓

Participants who withdraw within one year will be asked to have MRI at month 12; patients who withdraw after one year will be asked to have MRI straight away. MRI: magnetic resonance imaging; WOMAC: Western Ontario McMaster Universities Osteoarthritis Index; 25-(OHD)D: 25-hydroxy-vitamin D; FFQ: food frequency questionnaire.

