## Discussion

We have proposed this protocol to determine if vitamin D supplementation can slow disease progression in patients with knee OA. Vitamin D may have beneficial effects for the treatment of OA, although there are currently no recommended guidelines for this approach 
[48]. Hence, well-designed randomized controlled trials are required to test if vitamin D has disease-modifying and pain-relieving effects. Such studies also need an appropriate follow-up period to capture joint structural changes using objective measurements over the course of OA, and this has been incorporated into the design of the VIDEO study.

Assessing disease-modifying effects on OA requires an accurate measurement tool that is able to evaluate improvements in cartilage and joint health. Radiographic assessment of OA is two-dimensional, lacks sensitivity for changes over a short period and is highly susceptible to measurement error through factors such as variation in joint positioning 
[49]. MRI allows direct, accurate and reliable assessment of joint structural changes over time. These structural changes include cartilage loss, cartilage defects, increased tibial bone area, subchondral bone marrow lesions, meniscal tears and meniscal extrusion. Almost all these structural changes are predictive of total knee replacement 
[45,50,51], suggesting they are clinically relevant. Simultaneously, we will assess change in knee pain over time using WOMAC as a co-primary endpoint. Thus, the findings from this study will show whether vitamin D supplementation has both disease-modifying and symptom-relieving effects.

As suggested by the 2011 Endocrine Society Clinical Practice Guideline, all adults aged 50 to 70 years, and those over 70 years old require at least 600 and 800 IU/d of vitamin D respectively, to maximize bone health and muscle function. To raise blood levels of 25-(OH)D above 75 nmol/liter (the lowest sufficient threshold) requires at least 1500 to 2000 IU/d of supplemental vitamin D 
[52]. Thus, our study design provides a dose of 50,000 IU monthly to achieve serum 25-(OH)D levels above 60 nmol/liter in all compliant subjects 
[53]. This method will be less costly and will be more convenient than daily treatment. Toxicity is extremely unlikely with this dose.

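### The per-protocol set is defined by a month-3 serum level that says nothing about adherence in the placebo arm, so the analysis is either sparse and atypical in placebo or compares treatment responders with unselected controls

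*Protocol article*

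**What the plan says.** The Analysis plan names two analysis sets: "Both intention to treat and per protocol analyses will be utilized". It gives neither priority and defines the second by one laboratory value: "Per protocol will be defined as achieving a 25-(OH)D level > 60 nmol/liter at month 3". The definition names no arm and contains no adherence criterion.

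Four other places bear on it:

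- Inclusion criteria: entry requires "serum 25-(OHD)D > 12.5 nmol/liter and < 60 nmol/liter", in both arms.
- Intervention: "patients in the control arm will receive an identical inert placebo provided by the same company". Patients also record their medication in diaries.
- Discussion: the monthly dose is intended "to achieve serum 25-(OH)D levels above 60 nmol/liter in all compliant subjects".
- Table 1, Other measures: "Pill counts and adverse events" are scheduled at month 0 and at every later visit. Neither the counts nor the diaries enter the per-protocol definition.

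**The concern.** A per-protocol set should hold patients who followed the protocol, judged the same way in each arm. Here a placebo patient who takes every capsule starts on the failing side of the cut-off and receives nothing meant to move them across it. Those who do qualify get there through sun, diet, their own supplements or assay variation.

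The month-3 level is also a post-randomisation value that treatment itself changes. Selecting on it gives up the protection of randomisation, and the selection is plausibly related to outcome: the Background reports that "higher baseline serum levels of 25-(OH)D predicted reduced loss of cartilage volume over 2 years". Because the article ranks neither analysis above the other, a per-protocol result that disagreed with intention to treat could be read as evidence for or against the treatment when it reflects who was kept.

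**Working it through.** **1. The plan's own figure.** Inputs from Table 2 and the Sample size section: difference 2.16%, SD 6.5%, α = 0.05 (taken as two-sided), β = 0.20.

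n per arm = 2 × (1.960 + 0.842)² × 6.5² / 2.16² ≈ 142.2, rounded up to 143. The table states 143, so the sample size is not in question.

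With 200 per arm and 20% dropout, 160 per arm remain. SE = 6.5 × √(2/160) = 0.727; 2.16/0.727 = 2.97; power = Φ(2.97 − 1.96) ≈ 84%.

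**2. What the text implies without any assumption.**

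| Step | Vitamin D arm | Placebo arm |
|---|---|---|
| Level at entry | below 60 | below 60 |
| Treatment meant to raise the level | yes | no |
| Level intended if compliant | above 60 | none stated |
| Month-3 level > 60 as a sign of adherence | possible | no link |

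**3. The rule applied to both arms, as written.** The article gives no placebo distribution at month 3, so everything here except the eligibility limits is assumed: baseline normal with underlying mean 38–42 and SD 11, truncated to 12.5–60; mean placebo change 0 to +10 nmol/liter; SD of change 10–15. Simulation then puts about 6–31% of placebo patients above 60.

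- 6% of 160 = 9.6 placebo patients. Against all 160 treated patients, SE = 6.5 × √(1/9.6 + 1/160) = 2.16; power = Φ(2.16/2.16 − 1.96) ≈ 17%.
- 31% of 160 = 49.6 placebo patients. SE = 6.5 × √(1/49.6 + 1/160) = 1.056; power = Φ(2.16/1.056 − 1.96) ≈ 53%.

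Keeping all 160 treated patients is the favourable case. If 80% of them (128) qualify, the range is about 17–51%.

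The placebo patients kept are also unlike the rest. Under a somewhat wider set of assumptions (underlying mean 36–45, SD 12–14, change SD 8–15, the same range of mean change), their mean baseline is about 45–54 nmol/liter against about 36–43 in all placebo patients.

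**4. The rule applied to the vitamin D arm only.** The text does not state this reading. It sets treated patients who reached the level against placebo patients selected on nothing. How strong the selection is depends on the rise produced by the trial's dose. The only rise in the article, 27 nmol/liter, is for 400–800 IU/d, whereas 50,000 IU monthly is about 50,000 × 12/365 ≈ 1,640 IU/d. With the baseline assumptions of step 3 and a change SD of 12–15:

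| Assumed mean rise (nmol/liter) | Treated patients passing | Excess baseline of passers over the whole arm (nmol/liter) |
|---|---|---|
| 27 | 60–70% | 3.0–4.0 |
| 40 | 84–91% | 1.2–1.7 |
| 50 | 94–98% | 0.4–0.7 |

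The selection runs from appreciable to slight, and the article does not say where in this range the trial lies.

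**The case against.** The strongest defence is the Discussion. If the dose really brings every compliant patient above 60, the cut-off is a biochemical adherence check, and more objective than a pill count. That stands for the vitamin D arm, as far as the premise holds. It does nothing for placebo, where a level below 60 is what correct adherence should produce.

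Second, intention to treat is also planned. This stands in full: the randomised comparison, both co-primary endpoints and the sample size are untouched. Power is likewise a secondary complaint about a set never used for sizing.

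Third, the multivariable models adjust for baseline 25-(OH)D. That helps with the most obvious imbalance. The planned t-tests and univariate models do not adjust, however, and baseline adjustment does not fully remove selection on a post-randomisation value.

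Three stronger readings are tempting and are not supported:

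- *The placebo set will be almost empty.* The article gives no month-3 placebo distribution, and plausible assumptions allow up to about 31%. Sparse and atypical is as far as one can go.
- *The bias can be stated as a share of the target effect.* Spreading 2.16% over 27 nmol/liter gives 0.08% per nmol/liter, and the excess baselines in step 4 would then be worth 0.24–0.32 points (11–15% of 2.16) at a rise of 27, or about 0.09–0.13 points (4–6%) at a rise of 40. But the Sample size section derives that slope for a change in level, not for a difference in baseline, and the rise at this dose is not given. No single figure is defensible.
- *The exposure contrast disappears.* Two groups above 60 at month 3 can still differ in level, then and later.

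**Conclusion.** The definition is faulty under either reading. That follows from the entry criterion, the inert placebo and the wording of the rule, with no outside figure. Applied to both arms, it drops most adherent placebo patients; the sizes (about 6–31% kept, roughly 17–53% power against 84%) rest on the assumed distributions and show order of magnitude only. Applied to the vitamin D arm alone, it is a responder comparison with a bias of unknown size.

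Severity is moderate. A reader might infer that the trial's main result is compromised; it is not, because intention to treat does not use this rule. Nor is this a detail left to a later analysis plan: the article itself fixes the definition.

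**What to change.** Define the per-protocol set by criteria that mean the same in both arms: eligibility met, and a pre-set share of capsules taken (80%, for example) according to the pill counts and diaries. State that the rule applies identically to both arms, and fix the threshold before unblinding.

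Two conditions that might seem natural should be left out. A ban on off-study vitamin D cannot be a criterion, because the article states none during follow-up; the Exclusion criteria cover only supplements in the 30 days before entry. A compulsory month-24 MRI does not fit the Withdrawal section, which plans MRIs for those who leave early, and has no bearing on WOMAC.

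If the effect of reaching more than 60 nmol/liter is of interest, report it separately as exploratory and not as per protocol, for example as a complier average causal effect with randomisation as the instrument. That analysis assumes assignment acts only through crossing the cut-off, which is doubtful if smaller rises also matter, so the assumption should be stated.

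The cost is a small change of wording and no new data. Because the Quality assurance section says protocols will not be altered during the study, the change should be dated and documented. The real downside is that pill counts are a less objective measure of adherence than a serum level.

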**Co-primary outcome measure**						
MRI (cartilage volume changes)		✓				✓
WOMAC		✓	✓	✓	✓	✓

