### Withdrawal

If a participant withdraws or is removed from the study, the reason and date of discontinuation will be recorded. Any participant who withdraws within year 1 will be asked to have MRI at the end of year 1; participants withdrawing after year 1 will be asked to have MRI on leaving the study.

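### Carrying the last observation forward for all outcomes does not fit a co-primary scanned only at months 0 and 24: read literally, it enters zero cartilage loss, and the WOMAC mixed model does not need it

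*Protocol article*

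**What the plan says.** The Analysis plan gives one missing-data rule: "The last observation carried forward method will be used in the analysis of all outcomes among patients who made at least one follow-up visit". It is limited to patients who did not complete the study.

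The outcomes under this rule are measured on different schedules:

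- **Cartilage.** The co-primary in Outcome measures is "MRI assessment of volume changes in knee cartilage from baseline to month 24". Table 1 schedules MRI at months 0 and 24 only.
- **WOMAC.** Table 1 schedules it at months 0, 3, 6, 12 and 24. Its primary analysis is a "repeated measures mixed model with terms for treatment, month, center and the corresponding baseline values as the covariates".

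The Withdrawal section, repeated in the Table 1 footnote, asks for an extra scan: "Any participant who withdraws within year 1 will be asked to have MRI at the end of year 1", and "participants withdrawing after year 1 will be asked to have MRI on leaving the study".

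The linear regression takes "annual changes in cartilage volume, cartilage defects, bone area and muscle strength as the dependent variables". Sample size cites an expected cartilage loss of 4 to 5% per year.

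**The concern.** A patient seen at month 3, 6 or 12 who then leaves without a further scan meets the stated condition, because the condition is a visit. That patient's last MRI is the baseline scan. Carrying it forward gives a change of exactly zero in a disease that the protocol expects to progress. Under the same rule the patient falls below the threshold in the secondary cartilage-loss analysis and counts as a non-progressor for bone marrow lesions and meniscal abnormalities.

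The arm with more such patients looks better preserved. The bias can therefore run either way, and the rule cannot be defended as conservative.

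For WOMAC, a likelihood-based mixed model already uses incomplete series, with validity under missing-at-random. Filling the gaps first adds no information and replaces that assumption with the less plausible one that scores stay constant after dropout.

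**Working it through.** **Inputs.** From Sample size and Table 2: placebo loss 4.5%, SD 6.5%, detectable difference 2.16% (so vitamin D loss 4.5 − 2.16 = 2.34%), α = 0.05 (taken as two-sided), 80% power, 200 per arm, 20% dropout. The share *f* of an arm with a visit but no follow-up MRI is not given. Setting *f* equal to the whole dropout share is an upper bound.

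**The plan's own figure.** n per arm = 2 × (1.960 + 0.842)² × 6.5² / 2.16² = 142.2, which rounds up to 143, as in Table 2.

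**Observed scans only, 20% dropout.** With 160 per arm, SE = 6.5 × √(2/160) = 0.727 and z = 2.16 / 0.727 = 2.97. Power is 84.4%.

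**Effect of carrying the baseline scan forward.** With a share *f* set to zero change in an arm with mean *m*:

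- mean = (1 − f) × m
- variance = (1 − f) × 6.5² + f(1 − f) × m²
- SE of the difference = √[(v₀ + v₁)/200]

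For equal *f* = 20%:

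- Means: 0.8 × 4.5 = 3.60 and 0.8 × 2.34 = 1.872, so the difference is 1.73.
- Variances: 37.04 and 34.68, so SE = 0.599 and z = 2.89.
- Power is 82.3%.

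With no true effect and equal *f*, the expected difference is zero and the type I error stays at 5%.

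| Case (f placebo / f vitamin D) | True difference | Expected difference | SE | Result |
|---|---|---|---|---|
| 20% / 20% | 2.16 | 1.73 | 0.599 | power 82.3% |
| 25% / 15% | 2.16 | 1.39 | 0.600 | power 63.6% |
| 15% / 25% | 0 | 0.45 | 0.608 | type I error 11.5% |
| 12.5% / 7.5% | 2.16 | 1.77 | 0.627 | power 81% |
| 7.5% / 12.5% | 0 | 0.23 | 0.631 | type I error 6.5% |

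Rows 2 and 3 assume a 10-point dropout imbalance and no withdrawal scans. Rows 4 and 5 keep that imbalance but assume that half the dropouts have a scan annualised over its true interval. With no true effect, the bias is 4.5 × (difference in *f*): 4.5 × 0.10 = 0.45 and 4.5 × 0.05 = 0.225.

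**Withdrawal scans.** If a month-12 scan were treated as month 24 and divided by two years, that patient's annual loss would be roughly halved. If it is divided by the true interval, nothing needs to be carried forward. The text does not say which applies.

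**WOMAC illustration.** All inputs here are assumed: correlation 0.6 between visits, a placebo response that fades by month 24, every patient seen at month 3, and dropout unrelated to outcome within an arm. It compares carried-forward endpoint change with maximum likelihood on observed data.

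- True effect 0.30 SD, 20% dropout in each arm: 0.275 SD carried forward, 0.303 SD by likelihood.
- No effect, 15% against 25% dropout: bias about 0.03 SD carried forward, about zero by likelihood.

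**The case against.** Four counter-arguments deserve weight.

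- **Zero loss is not stated.** No sentence says that a baseline scan is carried forward. A convention of carrying only post-baseline values would leave these patients out of the MRI analysis. That stands as a limit on the wording, but the protocol states no such convention and makes a visit the condition, so zero change is the literal result.
- **Withdrawal scans.** A reader might infer that a 12-month scan is carried to month 24. The documents do not establish this: the regression outcome is annual change, which is compatible with using the actual interval. The requested scans also reduce the number of patients affected. They are only requested, however, so some patients may have none.
- **Size.** The largest figures need every dropout to be unscanned and a 10-point imbalance that nothing in the documents predicts. This stands. In the planned equal-dropout case, power stays above the 80% target and is close to that on observed scans. The WOMAC effect in the illustration is small.
- **Intention to treat.** A reader might infer that patients with no follow-up visit are removed from the intention-to-treat analysis. The sentence says only to whom carrying forward applies. It removes nobody, and this is not part of the point.

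That a statistical analysis plan may exist is no answer, because the protocol fixes this method itself.

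**Conclusion.** The point holds as a badly chosen rule that the protocol states, not as missing detail. Applied literally to an outcome with two scheduled scans, it turns an absent scan into no disease progression. Applied before the WOMAC mixed model, it is unnecessary and mildly harmful.

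With equal dropout the consequence is attenuation of the cartilage effect by the share affected, at most 20% at the planned dropout, with about two points of power lost against observed scans and no false-positive inflation. Serious harm to power or type I error requires unequal missingness. That cannot be excluded in advance, but the documents give no figure for it. The 64% power and 11% type I error are therefore upper-bound illustrations, not forecasts. With half the dropouts scanned, the same imbalance gives about 81% power and 6.5% type I error.

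**What to change.** Before unblinding, amend the Analysis plan as follows:

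1. Remove last observation carried forward as the main method. It may stay as a sensitivity analysis.
2. Analyse WOMAC with the stated mixed model on observed data.
3. Compute annual cartilage change over the actual interval between scans, using withdrawal MRIs at their real dates, and say so.
4. Handle absent follow-up MRIs by multiple imputation under missing-at-random, for the other MRI outcomes as well.
5. Add a missing-not-at-random sensitivity analysis, for example delta-adjusted.

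The cost is revised wording and modest extra analysis work. No new data are needed, and the article reports that recruitment was still under way.
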